**Figure 2 F2:**
[figure not shown]
Timeline of measured sick leave data of a potential participant.

The primary outcome measure described in our study is full RTW: i.e. duration of sick leave due to mental health problems in calendar days from the first day of sick leave to full return to work in own or equal earnings (table 1). In addition, the net return to work to own or equal work was measured. This is the net duration of sick leave due to mental health problems in hours of full work absenteeism from the first day of sick leave to full return to work with own or equal earnings. The difference with full RTW is that the hours of partial return to work and % contract working hours (36 hours = 100%) are converted into the number of hours of full work absenteeism [23]. This may result in a more precise measure of RTW, when compared to full RTW. As figure 2 shows, net and full RTW consider the time period between T0 and T3, in which data collection by questionnaires took place (figure 1).

**Table 1 T1:** Measured data and their instruments and timing of data collection

**Data**	**Instrument**	**Base-line**	**Follow up**			
**Data related to primary outcomes**		**T0**	**T1**	**T2**	**T3**	**T4**
Return to work						
Full Return to work	Database company	X			X	
Net return to work	Database company	X			X	
First (partial or full) return to work	Database company	X	X	X	X	
Time until 1^st ^recurrence	Database company	X				X
Number and days of recurrences of sick leave	Database company				X	X
Total days of sick leave during one year follow up	Database company	X			X	X
Treatment satisfaction						
Treatment satisfaction of employee	Questionnaire		X	X	X	
Treatment satisfaction of employer	Questionnaire		X	X	X	
Treatment satisfaction of the OP	Questionnaire				X	

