**Data related to prognostic measures**						

I) Personal characteristics						
Gender, Age	Database company	X				
Severity disorder: DASS/HADS (effect modifier)	Questionnaires		X			
Work-relatedness of the disorder	Medical files OHS	X				
Sick leave in year before inclusion (effect modifier)	Database company	X				
II) Treatment						
Treating occupational physician (OP)	Medical files OHS	X				
Diagnosis made by the OP	Medical files OHS	X				
Guideline adherence of the OP	Medical files OHS	X	X	X	X	
III) Work characteristics						
Type of function	Database company	X				
Number of working hours	Database company	X				
Police constabulary	Database company	X				

Another primary outcome variable that is part of the RTW process is first RTW: i.e. the duration of sick leave due to mental health problems in calendar days to first (partial or full) return to own or equal work. Other variables are related to recurrences of sick leave periods in the one year follow-up (T4)(table 1). These variables are the time in calendar days until the first recurrence of sick leave takes place and the number of and days during recurrences [21]. Total days of sick leave during follow-up is a primary outcome variables as well.

There was double registration of sick leave data, as both the employer and the OHS have their own registration system. The aim was to compare data of both systems, with the sick leave data of the employer as the 'golden standard'. This additional effort was done as reliable sick leave data are hard to get, since there is a known discrepancy with self-reported sick leave [24,25].

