### Data analysis

All analyses will be conducted according to the intention-to-treat principle and will be performed on the patient level. To examine the success of randomization, descriptive statistics will be used to compare the baseline measurements of the two groups. If necessary, analyses will be adjusted for prognostic dissimilarities.

The evaluations on the effectiveness of the guideline compared to usual care will be performed with two tailed tests at a significance level of 5% (P < 0.05). To examine differences in the data on RTW, we will use Kaplan Meier's and the Cox proportional hazard regression for recurrent events. The general idea behind this analysis is that the different time periods are analysed separately adjusted for the fact that the time periods within one patient are dependent. Recurrences of sick leave for any reason during follow-up will be added to the Cox proportional hazards model with the time to event approach, in which only the transitions from no treatment success (sick leave) to treatment success (full RTW) are taken into account [38].  In this model, the state of sick leave until the moment of inclusion will be added as a covariate. Number and days of sick leave periods in the year before inclusion will be added as a potential effect-modifier.

In a linear regression model treatment satisfaction during treatment (T2) and after treatment by the OP (T3) will be measured as respectively a short term and a long term effect and differences will be compared between the groups. Treatment satisfaction at the start of the treatment (T1) will be added as a covariate, even as the treatment group to examine differences in effects between the groups. The levels of treatment satisfaction of both the employees and their supervisors will be compared for the different moments with a chi-square test. Pair-wise correlations will be used to compare treatment satisfaction of the employee and their supervisor on the different moments.

In the Cox and linear regression models potential treatment differences by the OPs and their OHSs will be taken into account by means of nested dummy variables. The police constabulary the employee works for, will be put into the model as a binomial variable. Differences in sick leave patterns in the year before inclusion and in the severity of the mental health problems (DASS/HADS-scores) will be put into the model as potential effect modifiers.

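### The recurrent-events Cox model planned for return to work does not estimate the stated primary outcome: it mixes in absences of any cause and never counts a relapse against treatment

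*Protocol article*

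**What the plan says.** The Return to work section (text under Figure 2) defines the primary measure, full RTW, as "duration of sick leave due to mental health problems in calendar days from the first day of sick leave to full return to work". That is one episode with one cause. The same paragraph later says that "net and full RTW consider the time period between T0 and T3".

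The sample size section rests on a two-sided log-rank test with 90% power at the 0.05 level, for a difference of 0.25 in the proportion still on sick leave at one year. That is a comparison of one event per patient.

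For the analysis, the Data analysis section states that "we will use Kaplan Meier's and the Cox proportional hazard regression for recurrent events". It explains that "the different time periods are analysed separately adjusted for the fact that the time periods within one patient are dependent". It then adds all later absences, "Recurrences of sick leave for any reason during follow-up will be added to the Cox proportional hazards model with the time to event approach", and limits the event: "only the transitions from no treatment success (sick leave) to treatment success (full RTW) are taken into account". Sick leave up to inclusion enters as a covariate. Stratification by episode number is not mentioned.

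The text after Table 1 lists other RTW outcomes on recurrence: "These variables are the time in calendar days until the first recurrence of sick leave takes place and the number of and days during recurrences". It adds: "Total days of sick leave during follow-up is a primary outcome variables as well".

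**The concern.** The outcome and the sample size concern how quickly a patient leaves the mental-health episode that led to inclusion. The model instead asks how quickly patients leave any sick-leave spell, whatever its cause. Three consequences follow from the text.

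- The end of a brief absence for an unrelated illness counts as a success of a mental-health guideline.
- Going from work back to sick leave is not an event in this model, so a relapse is not penalised there.
- Only patients who have already returned to work can contribute later spells, so the mix of spells in each arm depends on what happened after randomisation.

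The resulting HR would be read as the answer on full RTW. It could show an effect where the index episodes do not differ, or shrink a real one.

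**Working it through.** **1. The plan's own figures.** With 107 per group and 20% dropout, 2 × 107 / 0.8 = 267.5, so the stated 268 follows. The 107 cannot be confirmed because the two one-year proportions are not given. Over all pairs 0.25 apart, the Freedman log-rank formula needs at most 86 per arm. Nothing below depends on this. The 107 is used only as the size of the simulated trials.

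**2. Relative length of spells.** Inputs from the sample size section (1999 police data): mental-health cases were 6.6% of registrations and 35.5% of sick-leave volume, averaging three months (taken as 90 days).

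- Ratio of mean lengths, mental-health to other: (35.5 / 6.6) / (64.5 / 93.4) = 7.8
- Mean other-cause spell: 90 / 7.8 ≈ 11.6 days
- Mean spell of any cause: 90 × 6.6 / 35.5 ≈ 16.7 days

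If participants' recurrences resemble the 1999 mix, most are much shorter than the index episode.

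**3. Simulation with no true effect.** Index spells are exponential with mean 90 days in both arms. Follow-up is 365 days, with 107 per arm and standard errors clustered by patient. Relapse rates are assumptions, since the article gives none. The pooled model restarts the clock at each spell and is not stratified. HR above 1 favours intervention, which is given the higher relapse rate.

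| Recurrent spells | Relapses per year, control vs intervention | Pooled HR | False positives (nominal 5%) |
|---|---|---|---|
| 1999 mix (6.6% at 90 days, rest at 11.6) | 1 vs 2 | 1.19 | 39% |
| 1999 mix | 1 vs 1.5 | 1.10 | 15% |
| Half are 90-day spells | 1 vs 2 | 1.08 | 11% |
| Half are 90-day spells | 1 vs 1.5 | 1.05 | 7% |
| All 90 days | 1 vs 2 | 1.00 | 5% |
| 1999 mix | 1 vs 1 | 1.00 | 7% |

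In the first row, other models give:

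- calendar-time Andersen-Gill: HR 1.17, 16% false positives
- gap-time model stratified by episode: HR 1.00, 5%
- Cox on the index episode only: HR 1.00, 4%

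With recurrences averaging 150 days the direction reverses (large-sample HR 0.94).

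**4. Simulation with a true effect.** The true index HR is about 1.5, recurrences follow the 1999 mix, and treatment is assumed not to change the length of later spells.

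- Equal relapse at 0.5, 1 and 2 per year: pooled HR 1.38, 1.32 and 1.24.
- At 1 per year, stratified by episode: HR 1.28.
- Relapse halved by treatment (2 to 1 per year): pooled HR 1.08, stratified 1.23.

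Stratifying by episode removes the false positive in step 3 but not the dilution. It averages the index effect with later episodes in which the HR is 1.

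**The case against.** A reader might infer that every relapse adds a success, so the arm with more relapses must look better. The documents do not support that. Each recurrence also adds time at risk, and one still open at one year is censored without an event. The model compares rates of leaving sick leave, not counts of successes. The upward bias needs three things together: recurrences shorter than index episodes, different relapse rates in the arms, and no stratification by episode. Take away any one and the no-effect HR returns to about 1.00.

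The relapse rates are assumptions. The article does not say whether the model is pooled or stratified, and it cites a method paper that may settle this. All of that stands, and it limits the claim about direction and size. It does not remove the mismatch with the outcome, or the dilution, which also appears under stratification.

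Relapse is also not ignored by the trial. Time to first recurrence, number and days of recurrences, and total sick-leave days are listed RTW outcomes, and Kaplan-Meier is named beside Cox. Extra sick days in one arm would show there, but none of these outcomes corrects the HR from this model.

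Finally, a reader might infer from the definition of full RTW that days before randomisation count as time at risk. The Data analysis section never says so. Entering earlier sick leave as a covariate fits a clock that starts at T0. What remains is that the two descriptions of the time window need reconciling.

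**Conclusion.** The point holds as a mismatch between outcome and model. The Cox model as written estimates neither the duration of the index mental-health episode nor the single-event comparison that was powered. This rests on the text alone.

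The size and direction of the consequence rest on assumptions. If recurrences resemble the 1999 all-cause mix and the model is unstratified, a relapse difference of 1 versus 2 per year gives an HR of about 1.2 with no true effect, and 1 versus 1.5 gives about 1.10. With half the recurrences at 90 days these fall to about 1.08 and 1.05. With all at 90 days, or with equal relapse, the HR is 1.00.

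The dilution needs no relapse difference. At one relapse per year in both arms, an index HR of about 1.5 becomes about 1.3, stratified or not, provided treatment leaves later spells unchanged.

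Because this model supplies the main RTW estimate, the plan should be corrected.

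**What to change.** - **Primary analysis:** Kaplan-Meier with log-rank test, and Cox regression, for the index mental-health episode only, from T0 to first full RTW, censored at T0 plus one year. Keep sick leave before inclusion as a covariate, as already planned.
- **Time window:** reconcile the two descriptions of full RTW in the Return to work section with this T0 origin.
- **Secondary analysis:** keep the recurrent-events model, stratified by episode, with the cause of each spell distinguished and the move from work back to sick leave modelled as well. Read it beside total sick-leave days and the recurrence outcomes already listed.

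The cost is a change of wording. The sick-leave outcomes already come from the company database, so no new data collection is foreseen. The small downside is that the recurrent-events model loses its primary place.

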#### Treatment satisfaction

Treatment satisfaction is a relevant outcome measure in occupational health care and therefore another primary outcome [26]. Higher patient satisfaction is related to better patient compliance and can improve the quality of OHSs. To date, most researchers assume that patient satisfaction is best defined as a patient's evaluation of aspects of a health care service based on the fulfilment of patient expectations. Since patients, employers and health care providers (OPs) are all involved stakeholders in the RTW process, it is important to measure the treatment satisfaction of all of these stakeholders.

Patient and employer satisfaction were measured using a short version of the Patient Satisfaction with Occupational Health Professionals Questionnaire [26]. This questionnaire was designed specifically for measuring satisfaction with occupational health care. It was designed in previous research on the quality of rehabilitation of cancer survivors [27] and transferred to occupational health care in another study on employees with mental health problems [18]. The 13 items of this questionnaire refer to (a) satisfaction in general (2 items), (b) interpersonal approach (4 items), (c) communication manner (2 items), (d) professional knowledge (5 items), and (e) total satisfaction of the treatment by the OP (13 items). Respondents answered on thirteen statements on a 5-point Likert scale: 'totally disagree – disagree – no opinion – agree – totally agree' (table 2). Because a higher score indicates more treatment satisfaction, item 3,4,9,10 and 12 will be recoded. The patient satisfaction questionnaire was adapted to the situation of the employer, to measure the treatment satisfaction of the supervisor (table 3).

**Table 2 T2:** Treatment satisfaction questionnaire employee

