### Data collection

The participants had to complete the mental health questionnaires (DASS, HADS) on the moment (T1) after they signed the informed consent (T0) (figure 1) (table 1). At the same time a questionnaire had to be filled in about their satisfaction with the treatment of the OP (T1). This questionnaire was sent again to the participant by the researcher (DR) after their second consultation with the OP (T2) and after the last consultation with the OP, at the moment of full RTW (T3). If T2 and T3 happened at the same moment, T2 was considered as T3. The questionnaires were returned to the researcher after completion in pre-stamped envelopes. The same was done for the supervisors of the participants, who received a questionnaire about their treatment satisfaction at the same moments (T1, T2 and T3). The OP received for each participant after the moment of full RTW another questionnaire to assess their treatment satisfaction (T3).

Baseline characteristics of the participants such as gender, age, marital status, work characteristics (type of function, hours working, part/full time), sick leave data and costs of work incapacity of the participants were gathered from records of the police constabularies, the latter after one year follow-up. Data about direct costs of treatment and medication of the employee were obtained after one year follow up from the insurance company of the police, the DGVP.

Guideline adherence and the according performance were based on data of the medical files of the participant, gathered from the databases of the participating OHSs. The data of the medical files were made anonymous and were transferred to an Access database, to select the relevant data of the medical files.

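### The chi-square test planned for employee and supervisor satisfaction assumes independent ratings, but the ratings are matched and repeated; the correlations cannot show a difference in level

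*Protocol article*

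**What the plan says.** All of the following is in the Protocol article.

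- **Status (Treatment satisfaction).** "Treatment satisfaction is a relevant outcome measure in occupational health care and therefore another primary outcome". It is to be measured for employee, employer and OP.
- **Scale (Treatment satisfaction).** "Respondents answered on thirteen statements on a 5-point Likert scale", giving four subscales and a total. Tables 2 and 3 tie both the employee form and the supervisor form to the last consultation that this employee had with the OP.
- **Timing (Data collection).** Participants answer at T1, T2 and T3. The same holds for the "supervisors of the participants, who received a questionnaire about their treatment satisfaction at the same moments (T1, T2 and T3"). A further rule merges moments: "If T2 and T3 happened at the same moment, T2 was considered as T3".
- **Between-arm analysis (Data analysis).** Linear regression at T2 and at T3, with T1 satisfaction and treatment group in the model.
- **Level comparison (Data analysis).** The satisfaction levels of employees and of their supervisors "will be compared for the different moments with a chi-square test".
- **Employee and supervisor together (Data analysis).** "Pair-wise correlations will be used to compare treatment satisfaction of the employee and their supervisor on the different moments".

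Tests are two-sided at 5%. For return to work, the same section says that periods within one patient are dependent and adjusts for this. It says nothing comparable for satisfaction.

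**The concern.** An ordinary chi-square test compares counts from independent observations. Here a participant and that participant's own supervisor rate the same OP's handling of the same case, and each rater answers up to three times. Employee v supervisor is therefore a matched comparison, and T1 v T2 v T3 is a repeated one. The standard error built into the test is wrong in both.

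Two lesser faults come with the chi-square. It treats ordered categories as unordered, and it yields a p-value without the size of a difference. The paragraph also does not define the levels it would tabulate, although the regression just before it treats satisfaction as a continuous score.

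The correlations have a different weakness. They respect the pairing, but the text gives them the job of comparing the two raters. A correlation describes whether the ratings move together and says nothing about whether one group is more satisfied.

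At stake is whether the planned stakeholder and time comparisons of a declared primary outcome have correct error rates and can show a difference that exists.

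**Working it through.** The plan states no figure for this analysis, so there is none to reproduce. The check has four steps.

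**1. Which readings are open, and is the test valid under each?**

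| Reading of the sentence | Data structure | Ordinary chi-square valid? |
|---|---|---|
| Employee v supervisor at each moment | Matched pairs | No |
| T1 v T2 v T3 within one type of rater | Repeated measures | No |
| Arm v arm at each moment | Independent groups | Yes |

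The third reading is the least natural. The sentence names no arm, and the sentences before it already give the arm contrast to linear regression.

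**2. Size of the error at one moment.** Inputs from the article: two-sided 5%, and 107 per group from the sample-size section, used here as 107 pairs. Assumptions, because the article gives no correlations or satisfaction rates: satisfaction is dichotomised from a bivariate normal score with latent correlation ρ of 0 to 0.7, with 50% satisfied in both groups (no difference) or 50% v 62% (difference). Results from 20,000 simulated trials per setting:

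| ρ | True level, chi-square | True level, McNemar | Power, chi-square | Power, McNemar |
|---|---|---|---|---|
| 0 | 4.8% | 5.0% | 41% | 42% |
| 0.3 | 2.8% | 5.0% | 41% | 50% |
| 0.5 | 1.5% | 5.0% | 40% | 57% |
| 0.7 | 0.6% | 5.0% | 38% | 70% |

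With 214 pairs (both arms) and ρ of 0.3 / 0.5 / 0.7, the chi-square level is 2.6% / 1.5% / 0.5%. Power is 72% / 74% / 77% for chi-square and 79% / 86% / 94% for McNemar.

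A closed form agrees. For a score cut at its median, the correlation of the two yes/no ratings is φ = (2/π)·arcsin(ρ). The difference in proportions then has (1 − φ) times the variance that the chi-square assumes, so the true level is 2·P(Z > 1.96/√(1 − φ)).

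- ρ = 0.3: φ = 0.194, 1.96/0.898 = 2.18, level 2.9%
- ρ = 0.5: φ = 0.333, 1.96/0.816 = 2.40, level 1.6%
- ρ = 0.7: φ = 0.494, 1.96/0.712 = 2.75, level 0.6%

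The same logic applies to two moments for one type of rater, with ρ as the between-moment correlation.

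**3. If the three moments were pooled as independent.** Employee v supervisor, 107 cases, three ratings per rater all counted as separate, no true difference, 10,000 simulated trials. The correlations are again assumed. The variance ratio is 1 + 2φw − 3φb, where φw applies within a rater and φb between the two raters.

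| Latent correlation within / between raters | Variance ratio | Closed-form level | Simulated level |
|---|---|---|---|
| 0.5 / 0 | 1 + 0.667 − 0 = 1.667 | 12.9% | 13.8% |
| 0.5 / 0.3 | 1 + 0.667 − 0.582 = 1.085 | 6.0% | 6.8% |
| 0.7 / 0.3 | 1 + 0.987 − 0.582 = 1.405 | 9.8% | 9.8% |

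In these settings the test is too liberal. The ratio exceeds 1 only when 2φw is greater than 3φb, so the direction depends on correlations that the article does not give.

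**4. What a correlation can show.** In one simulated set of 107 pairs the correlation was 0.517. Subtracting 1 point from every supervisor score left it at 0.517, while the mean employee-minus-supervisor difference moved from 1.644 to 2.644.

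**The case against.** The strongest reply has four parts.

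- **The sentence may mean arm v arm.** It follows a statement about differences between groups, and the next sentence deals with employee and supervisor separately. Under that reading the chi-square is valid. This stands as a possibility, but the regression already covers that contrast and the sentence mentions no arm. The ambiguity needs resolving in any case.
- **The article does not say which chi-square.** McNemar's statistic also has a chi-square distribution, and a condensed article may leave the variant to the full plan. That is fair as far as it goes, but an unqualified chi-square test is ordinarily taken as the independent-samples one, and no paired method is named.
- **It is a side analysis.** The second hypothesis is that the intervention yields more satisfaction than usual care, and the regression tests this. Employee v supervisor is not a stated hypothesis. This stands and limits the weight of the point.
- **A paired difference has its own problem.** The two questionnaires are not identical. Item 4 reverses its perspective, and item 10 asks about different problems. This also stands, as a caution in interpreting differences in the total score.

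A reader might infer that both methods ignore the pairing and that neither addresses difference. The text does not support that: correlations use the pairing, and a chi-square does test a difference in distribution. Nor does the article say that the 13-item total will be cut into categories. It speaks only of levels, which could refer to items or subscales.

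**Conclusion.** The point holds under the two natural readings. An ordinary chi-square does not fit matched or repeated satisfaction ratings, and the correlations cannot supply the missing comparison of levels.

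For a comparison at one moment with positively correlated raters, the test is conservative. Under the assumed correlations of 0.3 to 0.7 and 107 pairs, the true level is about 2.8% down to 0.6%, and power is 9 to 32 percentage points below McNemar's test (50 − 41 = 9; 70 − 38 = 32). If moments were pooled as independent, the level was about 7% to 14% in the settings simulated. It would therefore be wrong to infer that the p-values must be too large: the direction depends on the reading and on correlations that are not given. All sizes rest on a dichotomised score and assumed correlations and proportions.

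It would equally be wrong to conclude that the trial's main satisfaction result is at risk. The between-arm regression does not use this test. This is a correction to a supportive analysis, worth making because it is simple and replaces a misfitting test by one with a valid error rate and an estimate.

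**What to change.** 1. State which comparison is meant: employee v supervisor, change between moments, or both.
2. Replace the chi-square by paired differences with 95% CI. Alternatively, fit one linear mixed model with rater, moment and arm as fixed effects and random effects for the case and for the rater within the case. The model can also use cases without a separate T2 because it was relabelled T3.
3. If scores are categorised, define the categories and use McNemar's test or a test of marginal homogeneity.
4. Keep the pair-wise correlation only as a measure of association. Add an intraclass correlation if agreement is the aim.
5. When reporting employee-supervisor differences in the total score, note that some items differ between the two forms, for example items 4 and 10.

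Cost: slightly more analysis work and a few changed sentences. No new data are needed.

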### Secondary outcome

#### Cost-effectiveness measures

Cost-effectiveness of the intervention is a secondary outcome and was evaluated from the employers and the health care insurance company's perspective (expenditures for the employer and insurance company, respectively), as they are responsible for covering the costs of sick leave and treatment [28]. Direct costs of health care treatment are (table 1): (a) consultations of OPs and other OHS-professionals, (b) consultations of the psychologists from DGZ, (c) consultations of general practitioners, (d) consultations of a psychiatrist and/or psychologist and/or alternative therapist not participating in the study, and (e) medication related to the treatment of mental health problems [29].

Indirect costs are not related to health care, but are costs as a consequence of absence from work because of sickness: sick leave, disability and or death of productive persons. Costs of lost productivity caused by (partial) sick leave due to mental health problems were calculated from the net number of days of sick leave and lost earnings, as provided by the employer. Since our study took place in occupational health care and since most costs were caused by sick leave, extra efforts were made to gather reliable data on sick leave [30].

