### Prognostic measures

Prognostic measures and potential confounders were searched for in the literature [16,31,32]. The following prognostic measures were selected and will be taken into account as potential confounders (table 1): I) personal characteristics: (a) gender, (b) age, (c) disorder severity, based on mental health symptoms (DASS, HADS), (d) work relatedness of sick leave on the moment of inclusion, e) total days of sick leave in the year before the inclusion (figure 1); II) treatment characteristics: (f) treating OP, (g) guideline adherence by the OP, (h) referral behaviour of the OP; III) work characteristics: (i) type of function (executive vs. administrative), (j) working hours (part-time vs. full-time), and (k) police department (Zaanstreek-Waterland vs. Hollands Midden).

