To assess whether protocol deviations will cause bias, the results of the intention-to-treat analyses will be compared to per-protocol analyses. A process evaluation will be done, based on the assessment of guideline adherence by means of performance indicators [18]. For each performance indicator potential effects on our primary outcomes will be measured.

Indirect costs can be calculated using the friction cost approach (friction period 122 days) and the human capital approach, based on income as provided by the employer or as derived from function, age and gender [30]. Bootstrapping will be used for pair wise comparison of the mean groups to calculate mean differences and confidence intervals in costs and cost-effectiveness ratios for all interventions. All these analyses will be conducted in SPSS 14.0, Excel and, if necessary, in Strata.

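### The cost bootstrap compares group means with no named covariate although pre-treatment pay scales most of the cost, so the interval is valid but usually wider than it need be

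*Protocol article*

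**What the plan says.** Under Cost-effectiveness measures, productivity costs "were calculated from the net number of days of sick leave and lost earnings, as provided by the employer". The same section says that extra effort went into the sick-leave data, partly "since most costs were caused by sick leave". It also lists direct costs (consultations, medication), which pay does not scale.

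Under Data analysis, "Indirect costs can be calculated using the friction cost approach (friction period 122 days) and the human capital approach", with the rate "based on income as provided by the employer or as derived from function, age and gender". The comparison follows: "Bootstrapping will be used for pair wise comparison of the mean groups to calculate mean differences and confidence intervals in costs". The same sentence applies the bootstrap to cost-effectiveness ratios.

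The covariates named under Data analysis (physician and service, police department, prior sick leave, severity) are attached to the Cox and linear regression models. A general clause near the start of that section reads "If necessary, analyses will be adjusted for prognostic dissimilarities". The list under Prognostic measures includes age, gender, type of function, working hours, police department and "total days of sick leave in the year before the inclusion". Income is not on it. The Randomisation section describes blocks of 50 and names no stratification factor.

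**The concern.** Pay and contract hours are set before randomisation and the guideline cannot change them. They multiply the priced absence, so two arms with identical absence will show different costs if one happens to contain better-paid staff. Nothing in the stated design balances pay. A bootstrap of group means carries that variation into the interval, although the baseline data needed to remove much of it come from employer records that the trial already uses.

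The third hypothesis is that the intervention reduces costs, and this bootstrap is the only cost comparison the article describes. The sample size was set for return to work and nothing is stated about precision for costs, so a cheap gain in precision is worth having.

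**Working it through.** The article gives no cost SD, pay SD or interval width, so there is no cost figure to reproduce. The size below depends on assumed inputs.

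**Inputs from the article**
- Mean absence of about three months per case (sample size section), taken as 91 days.
- 250 envelopes (Randomisation), so 125 per arm. The standard-error ratios do not depend on this number.
- Friction period of 122 days and follow-up of one year, treated as caps on priced absence.

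**Assumed inputs**
- Exponential durations.
- Pay CV 0.1 to 0.4.
- 20% of staff part-time at 60% of full hours.
- Pay unrelated to absence, except where stated.

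**Step 1: variation in the earnings rate.** For contract hours, 1 + CV² = (0.8 + 0.2 × 0.36)/0.92² = 1.0302. With pay CV 0.3, the CV of pay × hours is √(1.09 × 1.0302 − 1) = 0.35.

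**Step 2: chance difference in pay.** SE = 0.35 × √(2/125) = 0.044, a 95% range of ±8.7%. With mean absence capped at one year of 89 days, that is 0.087 × 89 ≈ ±8 days' pay.

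**Step 3: the comparator.** With the same cap, absence has SD about 84 days. Chance variation in absence alone gives 1.96 × 84 × √(2/125) ≈ ±21 days. The two sources add in quadrature, so pay is the smaller one.

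**Step 4: effect on the standard error.** Let c be the CV of the earnings rate and h that of absence. If they are independent, CV²(cost) = c² + h² + c²h². Adjusting for the rate removes c², so

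SE ratio (adjusted/raw) = √[(h² + c²h²)/(c² + h² + c²h²)].

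At pay CV 0.3, c² = 0.123:
- One-year cap, h = 84/89 ≈ 0.94, h² = 0.886: √[(0.886 + 0.109)/1.118] = 0.943.
- 122-day cap, h ≈ 0.65, h² = 0.422: √[(0.422 + 0.052)/0.597] = 0.891.

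The formula covers productivity cost only. Direct costs that pay does not scale reduce the gain a little.

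**Step 5: simulation**

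| Setting | SE ratio, pay-adjusted/raw |
|---|---|
| One-year cap, pay CV 0.2 / 0.3 / 0.4, no correlation | 0.974 / 0.952 / 0.927 |
| 122-day cap, pay CV 0.1-0.4, no correlation | 0.87-0.96 |
| Pay-absence correlation −0.3 | about 0.96-1.00 |
| Pay-absence correlation +0.3 (107 per arm, pay CV 0.15-0.40) | 0.76-0.93 |

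In the one-year setting, adding prior-year leave, with an assumed correlation of 0.3, moves the first row to 0.939 / 0.920 / 0.896. A repeat of the first row with a small direct cost unrelated to pay agreed to within 0.01. Raw and adjusted differences had practically the same mean in every setting.

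**Step 6: what the ratio is worth.** A ratio of 0.952 is equivalent to 1/0.952² = 1.10, or about 10% more participants.

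**The case against.** The strongest reply is that nothing is wrong with the planned analysis. Under randomisation the raw difference is unbiased, and its bootstrap interval already contains the pay variation. From the employer's perspective, actual earnings are also a real part of the cost. All of this stands, so a reader who infers a biased saving or an invalid interval goes further than the article supports.

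Second, the general adjustment clause covers analyses at large, and the prognostic list contains function, age and gender, the same variables that would generate a derived pay rate, as well as working hours and prior sick leave. So it would be wrong to say that the plan cannot reach pay. What remains is that the clause is conditional on an observed imbalance, does not name income, and does not say how it would enter the bootstrap.

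Third, it is tempting to say that each person's own pay multiplies every absent hour. The article does not support that: the rate may be derived, friction costing stops at 122 days, and direct costs are unaffected by pay. A derived rate is still fixed before treatment, so the mechanism survives.

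Fourth, setting ±8 days' pay against a true saving of about 17 days (the mean difference at an assumed hazard ratio of 1.25, one-year cap) makes pay look dominant. The ±21 days from absence itself shows that it is not.

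Finally, a condensed article may leave the covariates of a secondary cost analysis to a fuller plan. This weighs against a high rating. The article does, however, specify covariates for its other models and a comparison of means for costs, so the choice it describes can fairly be commented on.

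**Conclusion.** The point holds as a modest precision improvement and nothing more. As described, the cost comparison leaves out a pre-treatment multiplier of most of the cost, and the interval is usually wider than necessary as a result.

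With pay unrelated to absence, adjusting for the earnings rate lowers the standard error by about 3-7% with a one-year cap (pay CV 0.2-0.4) and by roughly 4-13% under the 122-day cap (pay CV 0.1-0.4). If better-paid staff have shorter absences (correlation −0.3), the gain runs from near zero to about 4%; if they have longer absences, it is larger. Pay spread, part-time share, shape of the absence distribution and pay-absence correlation are all assumed, because the article reports none of them. Validity is not in question. Cost-effectiveness is a secondary outcome with no power claim, so the change is desirable and not essential.

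**What to change.** Keep the bootstrap. In each resample, estimate the cost difference as the arm coefficient from a regression of one-year cost on:
- arm;
- baseline earnings rate (income, or the derived rate, × contract hours);
- sick-leave days in the year before inclusion, as already listed under Prognostic measures;
- police department.

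Fix this list in advance, so that it does not depend on an observed imbalance. For the cost-effectiveness ratio, adjust the effect for the same covariates in the same resamples, so that an adjusted cost is not divided by an unadjusted effect. Report the raw mean difference and its interval beside the adjusted one.

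The cost is a few lines of code and no new data. The adjusted figure will differ slightly from the raw totals that the employer sees, and the gain may turn out small.
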